### Eligibility criteria

Women aged between 50 and 70 years living in the city of Ribeirão Preto, São Paulo, Brazil, with a previous diagnosis of SAH [3], will be recruited. Study participants must be physically inactive according to the Modified Baecke Questionnaire for the elderly (QBMI) [33]. We will consider the systolic blood pressure values between 120 and 159 mmHg or diastolic blood pressure values between 80 and 99 mmHg [34]. To be eligible to participate in the study, participants must have a diagnosis of post-menopause (amenorrhea for a period equal to or greater than 12 months) [35], have health conditions to practice physical activity according to the Physical Activity Readiness Questionnaire (PAR-Q), and not having a history of previous acute myocardial infarction or stroke confirmed by medical history, in addition to having no known allergy and/or intolerance(s) to nitrate, milk, and gluten. Those that interfere with the pH of the stomach (e.g., proton pump inhibitors) and/or using drugs that directly affect cardiac autonomic control (e.g., beta-blockers and calcium channel antagonists) will be excluded from the study. The other medications used by the participants will be recorded to be included as adjustment variables in the statistical analysis.

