### Interventions

#### Intervention description

The purpose of the study is to identify the effects of NO3 from beetroot juice, and therefore, the study was divided into two arms: (a) beetroot juice rich in nitrate and (b) beet juice without nitrate. The other protocols will be applied to the participants at the exact times and times of the day. In addition, because it is a crossover study, all participants will undergo all interventions equally.

Each protocol will last for 7 days, and its order of execution will be established through a randomization process. As this is a crossover study, each participant will participate in both protocols. Between one protocol and another, a 7-day washout interval will be given for the purification of the compounds provided by the protocols. Subsequently, the intervention contrary to the first will be provided, with the dynamics of the intervention being the same for both phases. Participants will receive eight units of juice bottles corresponding to the first intervention (placebo or nitrate) on the first laboratory visit. On the first day of intervention of each protocol, they will take two units (140 mL–800 mg of NO3), and from the second to the seventh day, they will take one unit (70 mL–400 mg of NO3) per day. Of the eight units (100%), six bottles (75%) will be destined for the participants to take home. On the seventh day of the intervention, the participants will take the last unit of juice at home and return to the laboratory for the last evaluation.

On the days that they do not visit the laboratory and on the last day of evaluation, the participants will drink the juice in the morning and on an empty stomach before brushing their teeth. After drinking the juice, we will ask them to take a 30-min break to consume breakfast. Photographs or videos of the participants ingesting the juice will be requested daily and sent to the researcher.

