Participants will not be informed about the order of administration of interventions. The researcher responsible for collecting and measuring the variables studied will also be blinded so as not to know which protocol will be administered. An independent researcher will be responsible for taking the juice and delivering it to the responsible researcher. In addition, another independent researcher/collaborator will be responsible for the statistical analysis of the data, so that he will be blinded so that he is not aware of which protocol order will be analyzed. Based on the steps previously described, the design of a randomized, triple-blind, placebo-controlled trial will be achieved. The quality of blinding will be assessed at the end of the study by asking each participant which beverage they believe they are ingesting in each of the two protocols.

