#### Initial evaluations

Participants will be identified by collecting the following information: age (years), body mass (kg), height (cm), body mass index (BMI), hip circumference (HC), waist circumference (WC), and circumference calf (CP). Anthropometric measurements will be obtained according to the recommendations described by Lohman et al. [38]. BMI will be calculated using the following formula: body mass (kg)/height^2^ (m). The waist/height ratio will be calculated by dividing the waist circumference by the height obtained in centimeters. The following assessments will also be carried out:Body composition: The fat percentage of the participants will be collected for a better characterization of the studied sample. The dual X-ray absorptiometry (DXA) will analyze the body composition, as lean body mass and fat mass. The exam will be conducted by a clinician trained in radiology at the Laboratory of Cineantropometry and Human Development [39].Familiarization of participants for the VO2peak test: A familiarization protocol will be used to improve the reliability of the data obtained with the VO2peak test. The participants will be physically inactive and will not be acclimated to the physical exercise, which may underestimate the values obtained in the test. At this stage, as a way of monitoring and safety of the participants, three collections of systolic and diastolic blood pressure will be performed before any procedure. On the first day, we will collect blood (15 mL) to analyze the blood glucose and lipid profile. We will use these data to characterize the sample. Prior to the VO2peak determination test, the participants will undergo a familiarization phase with the treadmill during three sessions performed on three different days. The Bruce protocol will be applied to determine the VO2peak. The values obtained during this phase will not be considered in the study [40].Determination of VO2peak (maximum exertion test): Another day will be scheduled to perform the VO2peak test of the participants so that the participants come to the laboratory in the fed state and with light clothes. The test will be performed on a treadmill (TPEE; Inbrasport ATL 2000®) using the Bruce protocol for the consequent use of 65–70% of the speed corresponding to the VO2peak for the load applied in the following steps. For VO2peak analysis, expired gases are analyzed in a commercial Teem 100 - VO 2000 system (Aerosport, Ann Arbor®, USA) previously validated by Novitsky et al. [41] and Wideman et al. [42] and periodically calibrated with volumes and gases of known concentration.

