### Assignment of interventions: allocation

#### Sequence generation and implementation

We will use the randomizer.org website to randomize the order of intervention that participants will receive. For each treatment, 16 “sets” (total number of participants) will be created with two treatment options, “number 1” or “number 2.” Each number refers to a type of protocol and, therefore, will be previously coded by a researcher who will not participate in the experiments and the treatment allocation order will be respected (e.g., set 1—number 1; set 2—number 1; set 3—number 2; [...] set 16—number 1). After the end of the first intervention, the participants will perform the opposite intervention (Fig. 3).

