### Statistical methods

For data analysis, descriptive statistics will be performed to characterize the sample. The results will be presented with mean and standard deviation values when the residual values of the variables present normal. Values in the median distribution and interquartile intervals will be presented when the residuals’ assumptions of normality and homoscedasticity are not reached. Data will be analyzed using linear analysis of mixed effects adjusted for age, drugs, and VO2peak, considering time and treatment as an independent variable. Per-protocol analysis will be performed to account for possible dropouts during the study. The analysis will be conducted according to the intention-to-treat principle. The generalized mixed linear model will treat the missing values, using maximum likelihood to estimate the model parameters. Differences in all tests will be considered significant when the *p* value is less than 0.05. The statistical program used will be RStudio (v. 1.0.136). The confidence interval at the 95% level will be exposed when we describe the comparison values of the variables with each other. The magnitude of significant differences will be quantified through effect size calculated using Cohen’s *d*. A large effect size will be considered for values greater than 0.9 and a medium effect size for values between 0.9 and 0.5 [54].

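### The stated crossover model leaves out period, and no rule is stated that balances the two treatment orders

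*Protocol article*

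**What the plan says.** All references are to the protocol article.

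- **Model.** Statistical methods describes a "linear analysis of mixed effects adjusted for age, drugs, and VO2peak, considering time and treatment as an independent variable". Neither period nor sequence is named as an analysis term there or elsewhere.
- **Design.** Under Intervention description, "each participant will participate in both protocols". Each protocol lasts 7 days. "Between one protocol and another, a 7-day washout interval will be given".
- **Order.** Sequence generation and implementation says: "We will use the randomizer.org website to randomize the order of intervention that participants will receive". Each of 16 sets receives option 1 or 2, and the other option follows in the second period. No block, and no requirement of equal numbers, is stated.
- **Covariates.** On drugs, Eligibility criteria says: "The other medications used by the participants will be recorded to be included as adjustment variables in the statistical analysis". On fitness, Initial evaluations says: "Another day will be scheduled to perform the VO2peak test". That visit comes before the interventions and is not repeated.
- **Analyst.** Intervention description blinds the analyst so that "he is not aware of which protocol order will be analyzed".
- **Target.** Sample size uses a 5 mmHg reduction with a variation of 4 mmHg, two-sided 95% confidence and 80% power. It reaches a minimum of 11 and plans to recruit 16.

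**The concern.** In a two-period crossover each woman supplies one nitrate-placebo difference. Anything constant within her cancels from it. A change between her first and second period that has nothing to do with the juice does not cancel: it adds to the difference in one order and subtracts in the other. A period term removes it.

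The listed terms do not. Age, recorded medication and a single pre-treatment VO2peak are constant within a woman. 'Time' is not defined, but the schedule under Exercise variables is in minutes of a session on days 1 and 7, and the two periods are called protocols or phases, so measurement time is the natural reading.

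If a period effect exists, two things follow. With unequal orders, part of it moves into the treatment estimate. With equal orders it leaves the estimate alone but swells the error term. Either way the primary blood pressure comparison loses sharpness for want of one model term.

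**Working it through.** **Set-up.** Assume complete data and one blood pressure value per woman per period. Write her nitrate-placebo difference as d = δ + πq + e. Here δ is the treatment effect, π the change from period 1 to period 2 unrelated to juice, q = +1 or -1 by order, and e has standard deviation SDdiff.

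**Inputs.** |δ| = 5 mmHg, variation 4 mmHg and N = 16 come from Sample size; the 16 sets come from Sequence generation. The documents give no π; the assumed values are 0, 2, 3 and 5 mmHg.

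**1. The plan's own figure.** If 4 is the within-woman SD, SDdiff = 4√2 = 5.66 and SDdiff² = 32. Then n = (1.960 + 0.842)² × 32 / 5² = 10.05, which rounds up to 11, as stated (13 with the t distribution). If 4 were SDdiff itself, n would be 6 (8 with t). I therefore use 5.66 as the main case.

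**2. Split of orders, if the 16 draws are independent at 1:1.**
- P(8:8) = 12,870 / 65,536 = 0.196
- P(10:6 or worse) = 2 × 14,893 / 65,536 = 0.454
- P(11:5 or worse) = 2 × 6,885 / 65,536 = 0.210

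**3. Shift in the estimate without a period term.** Shift = π × (n1 - n2) / 16. At 11:5 this is 6/16 = 0.375 × π: 0.75, 1.13 and 1.88 mmHg for π = 2, 3 and 5. Its average over all possible lists is zero.

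**4. Precision.** Without the term, over free draws, SE = √((32 + π²)/16). This is 1.41 at π = 0, 1.60 at π = 3 and 1.89 at π = 5. With the term, SE = ½√(32 × (1/n1 + 1/n2)), whatever π is: 1.41 at 8:8 and 1.53 at 11:5.

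**5. Power for 5 mmHg** (simulation, 20,000 trials per setting, N = 16, SDdiff 5.66).

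| π (mmHg) | Free draws, no period | Free draws, period | 8:8, no period | 8:8, period |
|---|---|---|---|---|
| 0 | 0.910 | 0.885 | 0.911 | 0.908 |
| 2 | 0.880 | 0.889 | 0.888 | 0.909 |
| 3 | 0.827 | 0.887 | 0.854 | 0.907 |
| 5 | 0.693 | 0.883 | 0.736 | 0.907 |

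**6. Type I error without the term.** Over free draws it is 0.049, 0.049 and 0.052 at π = 2, 3 and 5. Given an 11:5 split it is 0.061, 0.075 and 0.100. Given an 8:8 split it is 0.039, 0.028 and 0.009. With the term it is about 0.05 throughout.

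**7. Sensitivity.** With SDdiff = 4, power under free draws without and with the term is 0.988 and 0.993 (π = 2), 0.964 and 0.992 (π = 3), and 0.833 and 0.993 (π = 5). Type I error at 11:5 without the term is then 0.076, 0.094 and 0.100. The Abstract gives 25 women where Sample size gives 16. That is a separate conflict, and it changes little here: the expected absolute imbalance, |n1 - n2|/N, is 0.161 at 25 and 0.196 at 16.

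**The case against.** **The period effect is assumed.** This stands. No figure is given, and at 2 mmHg or less the loss is slight. A reader might infer a large effect from women new to the treadmill. The documents do not support that: Initial evaluations schedules three familiarisation sessions on separate days, and three blood pressure collections before any procedure. Some drift over two 7-day protocols and a 7-day washout remains possible, but its size is unknown.

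**There is no bias under randomisation.** This also stands. A reader might infer that the trial's false positive rate is inflated. It is not, over all possible lists: the 7.5% to 10% error applies only given a split such as 11:5, and at 8:8 the test is conservative.

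**Independent draws are an inference.** The worked example shows only four of the 16 sets and would also fit a balanced list. The split probabilities are therefore conditional. Step 5 shows that omission costs power even at 8:8.

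**The analyst may still have period.** A reader might take the blinding sentence to forbid fitting it. The sentence sits in a paragraph on blinding, and Who will be blinded describes coded interventions. Period with coded treatments is compatible with both, but the wording should say so.

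**Maximum likelihood.** A reader might add that "using maximum likelihood to estimate the model parameters" makes intervals too narrow. That phrase occurs where missing values are discussed and does not rule out the restricted form, which an analysis plan would normally settle. No point is made of it.

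**The article is condensed.** True, but it lists the model's terms. If a fuller plan contains period, the article's list needs correcting. Keeping the covariates does no harm to the treatment contrast; they simply do not do this job.

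**Conclusion.** The point holds as a should-fix. The stated model for a two-period crossover omits period, and no other listed term stands in for it on the natural reading of 'time'.

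The main cost is precision. At an assumed period effect of 3 to 5 mmHg, with 16 women and SDdiff 5.66, power is 83% to 69%. With the term it is about 88% under the same draws, and 91% if the orders are also balanced. If the realised split is 11:5, the estimate moves by 1.1 to 1.9 mmHg against a 5 mmHg target. If the period effect is below about 2 mmHg, little is lost.

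These sizes rest on three assumptions: the period effect itself, 4 mmHg read as the within-woman SD, and, for the split probabilities, independent draws. The omission of the term rests on the text alone.

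**What to change.** - Add period as a fixed effect, with random effects for participant and for participant within period.
- Define 'time' as measurement time.
- State that the blinded analyst receives the period of each record with treatments coded A and B, and that the code stays closed until the analysis is finished.
- State how the order list was restricted, if it was. For women not yet allocated, use randomly permuted blocks. Women already allocated keep their order, and the period term covers them.

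The model changes can be made at any time before unblinding. They cost one degree of freedom and a few lines of text, and no extra participants. If there is no period effect, power falls from 0.910 to 0.885 under free draws, and hardly at all when the orders are balanced (0.911 and 0.908).

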### Sample size

The number of participants in this study considered the most recent meta-analysis study, which found a reduction of 5 mmHg caused by beetroot juice rich in nitrate in patients with SAH as significant with a variation of 4 mmHg [10, 11]. We applied these values in the Hedwig Harvard Sample Calculator software online, considering a bilateral 95% confidence interval and a power analysis of 80% that provided a minimum of 11 participants for this clinical trial [29]. We will recruit sixteen postmenopausal women diagnosed with SAH to ensure a sufficient sample size after the interventions. This sample size is consistent with previous studies that investigated the effects of BRJ on BP in patients with SAH. The Amaral et al. [29] study used 13 postmenopausal women to examine the impact of BRJ on PEH. Broxterman et al. conducted two studies in patients with SAH medicated and non-medicated. In both trials, the sample was 13 and 14, respectively. The most recent investigation in this field conducted by Siervo et al. [53] used 16 patients with SAH.

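### Naming maximum likelihood as the mixed-model estimator makes nominal 5% tests run at about 6% with 16 women; REML with small-sample degrees of freedom avoids this (minor)

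*Protocol article*

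**What the plan says.** Under Statistical methods, outcomes are to be analysed by "linear analysis of mixed effects adjusted for age, drugs, and VO2peak, considering time and treatment as an independent variable". The estimator appears in the sentence on missing data, which leaves missing values to a generalized mixed model, "using maximum likelihood to estimate the model parameters". The testing rule is: "Differences in all tests will be considered significant when the *p* value is less than 0.05". The same section promises 95% confidence intervals. It does not mention REML, a random-effects structure, a degrees-of-freedom method or a reference distribution.

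On numbers, Sample size says: "We will recruit sixteen postmenopausal women diagnosed with SAH". Sequence generation and implementation also works with 16, but the Methods part of the abstract gives 25. Every woman receives both juices (Intervention description), so the treatment contrast is within-woman.

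**The concern.** ML estimates variances as if the fixed effects were known. The variance components are therefore biased downwards, and the bias grows as the sample shrinks. In a trial of 16 women this could make standard errors too small, intervals too narrow and p values too low for every outcome analysed this way, including blood pressure, the primary outcome. The bias always favours declaring an effect. Nor do missing values require ML, since REML keeps the same incomplete records under the same missing-at-random assumption.

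**Working it through.** **The plan's own figure.** Sample size takes "a reduction of 5 mmHg caused by beetroot juice rich in nitrate in patients with SAH as significant with a variation of 4 mmHg", "considering a bilateral 95% confidence interval and a power analysis of 80% that provided a minimum of 11 participants". With δ = 5 and 4 read as a standard deviation, n = 2 × (4 × (1.960 + 0.842)/5)² = 10.05, rounded up to 11. The stated minimum reproduces. The test sizes below do not depend on the 4 mmHg.

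**Inputs.**
- n = 16 women (Sample size; Sequence generation and implementation), with 25 as the alternative (abstract).
- Readings per woman, m (Exercise variables): one resting blood pressure and two after exercise on each collection day, two collection days per condition, two conditions. That gives 3 × 2 × 2 = 12, or 6 if the acute and 1-week parts are analysed separately.
- Two-sided 5% level.
- Assumptions, because the article does not give them: balanced data, a random intercept per woman, a treatment-by-time mean structure and a correctly specified covariance.

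**Variance ratio.** The residual sum of squares has (n − 1)(m − 1) degrees of freedom. REML divides by that number and ML divides by n(m − 1). The ratio is (n − 1)/n = 15/16 = 0.9375. The standard error ratio is √0.9375 = 0.968, which is 3.2% too small. At 25 women the variance ratio is 24/25 = 0.96 and the standard error ratio is 0.980.

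**Actual size of the nominal 5% test.** For critical value c, size = 2 × P(t_df > c × √ratio). Two examples at n = 16:
- m = 6, df = 15 × 5 = 75, t reference: 1.992 × 0.968 = 1.929, giving 5.75%.
- One difference per woman, df = 15, normal reference: 1.960 × 0.968 = 1.898, giving 7.71%.

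The likelihood-ratio test rejects when t² > df × (exp(3.84/N) − 1), with N = n(m − 1).

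| Layout | ML, t reference | ML, likelihood ratio | ML, normal reference | REML, normal reference |
|---|---|---|---|---|
| n = 16, m = 12 | 5.76% | 5.81% | 5.95% | 5.17% |
| n = 16, m = 6 | 5.75% | 5.86% | 6.16% | 5.37% |
| n = 16, one difference per woman | 5.68% | 6.19% | 7.71% | 6.88% |
| n = 25, m = 12 | 5.48% | 5.50% | 5.59% | 5.11% |
| n = 25, m = 6 | 5.47% | 5.53% | 5.72% | 5.23% |
| n = 25, one difference per woman | 5.44% | 5.73% | 6.68% | 6.17% |

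REML with a t reference on the correct degrees of freedom gives exactly 5% in the balanced case.

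The rows with one difference per woman apply when each condition contributes a single value. They also apply if women differ in their response to treatment (a woman-by-treatment random effect, again an assumption). The error then comes from 16 woman-level differences however many readings are taken.

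**Check by simulation.** Null data for 16 women, with age, drug and VO2peak covariates, 600 data sets per layout, normal reference:
- 2 readings per woman: ML rejected in 7.8%, REML in 6.8%.
- 6 readings per woman: ML rejected in 7.0%, REML in 6.0%.

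The Monte Carlo standard error is about 1 point, so these agree with the exact values. The standard error ratio was 0.968. The between-woman variance fell to about 0.73 to 0.74 of its REML value, but in balanced data it does not enter the treatment contrast.

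**The case against.** The strongest reply is that the sentence concerns missing data. It says incomplete records are handled through the likelihood, and a reader could take REML as included. A degrees-of-freedom method is also something a journal article properly leaves to the analysis plan. Part of this stands: the inflation is conditional on a literal reading, and the silence on degrees of freedom is not itself a fault. But the sentence states what ML is used for, namely estimating the model parameters, so it names an estimator. If REML was meant, the wording still needs correcting.

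A second reply is that the effect is small with the readings actually scheduled. That stands too, and it sets the size of the point.

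A reader might infer something stronger. Adding a period term (variance ratio 14/16) and a normal reference to a layout with one value per condition gives a size of 8.8% and an interval about 15% too narrow: 1.960 × √(14/16)/2.145 = 0.855. With 11 women the same construction gives 11.0%. The document does not support these figures as a description of the plan:
- The model as listed has no period term.
- No normal reference is stated. In the 0.855, ML accounts for a factor of √(14/16) = 0.935 and the normal reference for 1.960/2.145 = 0.914, so most of the narrowing does not come from ML.
- Eleven is the calculated minimum, not a forecast of completers. Statistical methods plans an intention-to-treat analysis in which the model handles missing values.

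Finally, the estimator is attached to a generalized mixed model. For an outcome that is truly modelled as non-normal, ML is the usual choice and the REML remedy does not carry over. The fix allows for this.

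**Conclusion.** The point holds in a modest form. If ML is used as written with 16 women, standard errors for the treatment contrast are about 3% too small. Nominal 5% tests then run at 5.8 to 6.2% with the 6 or 12 planned blood pressure readings and a random intercept. If the contrast rests on one difference per woman, the range is 5.7 to 7.7%. At the upper end, 1.9 of the 2.7 excess points come from the normal reference (REML with that reference already gives 6.9%) and 0.8 from ML. With 25 women the repeated-readings figures fall to about 5.5 to 5.7%. The conflict between 16 and 25 therefore changes the size of the problem but not its direction.

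These figures rest on balanced data, a correct covariance structure and a literal reading of the estimator sentence. It would go too far to say that the trial is committed to tests at 8 or 9%. Severity is minor. The correction is still worth making, because the bias runs one way and ML brings no offsetting benefit for missing data.

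**What to change.** For the linear mixed models, replace the reference to maximum likelihood in Statistical methods with: *using restricted maximum likelihood (REML), with Kenward-Roger (or Satterthwaite) degrees of freedom for tests and confidence intervals*. Both parts are needed, because REML with a normal reference still runs at 5.2 to 6.9% with 16 women. Keep ML only for any model that is truly generalized (non-normal outcome) and for comparing models with different fixed effects.

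The change is one phrase, needs no further data or participants, and can be done in R, the software already named. Incomplete records are kept under the same missing-at-random assumption. The price is slightly wider intervals and slightly larger p values. The change should be made before the treatment codes are revealed.
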